**Method and design:**

A quasi-experimental clinical trial will be conducted. The study is designed to include 212 BPD patients who will be non-randomly assigned to specialized health care services and to two TAU centers. Patients will be recruited at each site following the routine clinical pathways of referral at each center. The primary outcome measures are BPD severity, suicide attempts and hospital admissions. The secondary outcome measures will include measures of general psychopathology, psychosocial functioning, quality of life and retention in treatment. In addition. An economic evaluation from a societal perspective will be conducted.

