### Sample size

Based on the power analysis (power=0.90), we estimated that the sample size of our study should be 212 participants (106 people per group) to detect differences between the two clinical groups. The power calculation was based on a moderate effect size (Cohen’ s d= 0.45) due to the naturalistic character of the study. A recent meta-analysis (58) established this value of Cohen’s d, calculating the effect size for borderline symptom trials as either 0.31 or 0.56, depending on the stand-alone or add-on design. Accessing these data, the authors decided to set the effect size as 0.45, which is a moderate value that is neither strict nor lenient. Before we reach the aforementioned sample size, we start processing our data within subjects, where a smaller sample size of 158 participants (79 per group) is needed to obtain a significant power of 0.80. The software used to calculate the power was R version 4.0.3.

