2. *The second phase of the program consists of* sp*ecific interventions*. Clinical criteria (‘readiness for therapy’, self-harm, suicidality, emergency room visits, need for hospitalization, etc.) and availability (e.g., twice a year in therapy groups, once a year in the day hospital, while a small number of patients enroll each year in individual psychoanalytic psychotherapy) determine the assignment of patients to one (or more) of these interventions. The following specific interventions are available:

*Group psychoanalytic psychotherapy*: This is the main intervention, with a capacity of approximately 50 patients, in groups of 8–10 patients. It lasts for 3 years and offers one or two 90-minute sessions per week.
*Individual psychoanalytic psychotherapy*: capacity of 4–8 patients. It lasts for 2 years and offers one 45-minute session per week.
*Group or individual psychodynamic art therapy*: capacity of 4–12 patients. Last 2 years and offers one two-hour group session or one 60-minute individual session.
*Day hospital program*: The day hospital program can accommodate up to 9 patients. It includes a combination of group and individual psychotherapeutic interventions (psychoanalytic psychotherapy, art therapy, drama therapy) and psychiatric management. The day hospital program lasts 9 months. After their completion, the participants continued in group psychoanalytic psychotherapy for an additional 3 years.
*Parent groups or parent couples’ professional counseling*: parents of all-day hospital patients and a limited number of outpatients can participate in parent groups or parent couples’ psychoanalytic counseling. It lasts for one year and provides one 90-minute group or couples session per week.
*Psychiatric management and pharmacotherapy*, if required (1 session per month). Supervision is offered fortnightly for all psychotherapy interventions and weekly for psychiatric interventions.

During phase 2, in case of crisis, the patient contacts his/her psychotherapist or psychiatrist by telephone and, if necessary, goes to the emergency room of Eginition Hospital. In cases of hospitalization, the patient continues the program after discharge.

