#### Dropout rates

Dropout rates will be compared at the end of the study with the non-parametric criterion Mann Whitney (IV: group assignment and DV: number of drop outs), as number of drop-outs is an ordinal variable.

The Statistical Package for the Social Sciences (SPSS) version 25 (95) will be used for the statistical analyses. All significance tests will be two-tailed, with a 5% significance level and 95% confidence interval.

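### The 158 figure labelled within-subject is the between-group size for 80% power, the early processing it supports is undefined, and the 90% power for 212 assumes that every patient is analysed

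*Protocol article*

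**What the plan says.** The Sample size section sets "212 participants (106 people per group) to detect differences between the two clinical groups" at 90% power. On the effect size, "the authors decided to set the effect size as 0.45", a value between two estimates from a meta-analysis described as "calculating the effect size for borderline symptom trials as either 0.31 or 0.56". The abstract (Method and design) makes clear that 212 is the number entered, not the number left after losses: "The study is designed to include 212 BPD patients who will be non-randomly assigned".

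The same section then says that, before 212 is reached, "we start processing our data within subjects, where a smaller sample size of 158 participants (79 per group) is needed" for a power of 0.80. Under Dropout rates, "All significance tests will be two-tailed, with a 5% significance level and 95% confidence interval".

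Four other places bear on these figures:
- Design: follow-up is two years for all outcomes and three more years for the primary outcomes.
- Aims and hypotheses: the longer follow-up is restricted to the primary outcomes out of concern about losing participants.
- The STP-BPD, on group psychoanalytic psychotherapy: "This is the main intervention, with a capacity of approximately 50 patients, in groups of 8–10 patients".
- Evaluation of effect: a regression at each time point, adjusted for the baseline value, treatment duration, sessions attended and baseline confounders, then a repeated-measures ANOVA. No analysis at 158 and no separate within-subject test appears.

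**The concern.** A size given per group, at the same effect size as the main comparison and with lower power, looks like a between-group calculation under a within-subject name. If so, the article's only account of its early data processing does not match the number that justifies it. A reader cannot tell whether early work means change within each arm, which leaves the main comparison untouched, or a first look at the group difference at an unadjusted 5%.

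The main figure has a related weakness. The 90% power is quoted for the number enrolled, in a study lasting two to five years that plans to record and compare dropouts and treats part of one arm in therapy groups. If the calculation has no slack, the quoted power describes a trial in which nobody is lost and all patients are independent.

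**Working it through.** **Inputs from the article.** d = 0.45; two-sided alpha 0.05; 1:1 allocation; 106 per group at 90%; 79 per group at 80%; therapy groups of 8–10 with capacity about 50. **Assumed, because the article gives no value:** loss rate L, baseline-outcome correlation r, intraclass correlation ICC, and share s of the STP-BPD arm treated in groups.

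**1. Reproducing 212.** Two-sample formula: n per group = 2(z₀.₉₇₅ + z_power)²/d². At 90%: 2(1.960 + 1.282)²/0.2025 ≈ 104. The noncentral t gives 104.75, so 105. Power at 106 is 90.3%. The slack is one patient per arm.

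**2. Reproducing 158.** The same formula at 80%: 2(1.960 + 0.842)²/0.2025 ≈ 78. The noncentral t gives 78.49, so 79 per group, 158 in all. Power at 79 is 80.3%. This matches the stated figure exactly.

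**3. Testing the within-subject label.** Paired formula: n = (z₀.₉₇₅ + z_power)²/d_z², where d_z is the mean change divided by the SD of change.
- d_z = 0.45: 7.85/0.2025 ≈ 39; the t-based answer is 40.7, so 41 patients. A paired test on 79 would have 97.7% power, and on 158 more than 99.9%.
- If 0.45 is instead scaled to the raw SD, d_z = 0.45/√(2(1 − ρ)), with ρ the correlation between a patient's two measurements. At ρ = 0 this is 0.318, needing 79.5, so 80 patients. That is near 79, but only because zero correlation makes the paired variance equal the two-sample variance. At ρ = 0.5, d_z is 0.45 and the answer is 41 again.

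No paired calculation gives 79 without in effect removing the pairing, and the article states no pre-post effect or correlation.

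**4. If the groups were compared at both sizes.** The correlation of the two test statistics is √(158/212) = 0.863. For a bivariate normal, P(|Z₁| > 1.96 or |Z₂| > 1.96) = 0.0736, or about 7.4%.

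**5. Power of 212 under loss.** Evaluable n per group = 106(1 − L). Baseline adjustment replaces d by d/√(1 − r²): 0.472 at r = 0.3 and 0.520 at r = 0.5. Noncentral t:

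| Loss | n per group | Unadjusted | r = 0.3 | r = 0.5 |
|---|---|---|---|---|
| 0% | 106 | 90% | 93% | 96% |
| 20% | 84.8 | 83% | 86% | 92% |
| 30% | 74.2 | 78% | 81% | 88% |

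At 10% loss (95.4 per group), unadjusted power is 87%.

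**6. Clustering in the STP-BPD arm.** With groups of 9, that arm's variance is multiplied by v = 1 + s × 8 × ICC. Normal approximation, no baseline adjustment: power = Φ(0.45/√((v + 1)/n) − 1.96), with n as in step 5.

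| ICC | s = 1, no loss | s = 50/106, no loss | s = 1, 20% loss | s = 50/106, 20% loss |
|---|---|---|---|---|
| 0.01 | 89.5% | 90.1% | 81.9% | 82.7% |
| 0.05 | 84.9% | 87.9% | 76.3% | 80.0% |
| 0.10 | 79.1% | 85.2% | 69.7% | 76.7% |

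Without clustering this approximation gives 90.6% at no loss. Combining r = 0.5, ICC 0.05 and s = 1 gives 87% at 20% loss and 82% at 30%.

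**The case against.** **A reader might infer a hidden between-group interim analysis.** The documents do not support that. The early processing is announced openly and called within-subject, and no section plans a group comparison at 158. The authors may simply have used the wrong formula for descriptive early work, in which case there is no repeated look and no 7.4%. This stands, so the error rate must be stated conditionally. It does not rescue the number, which is wrong for the label it carries, and nothing in the text excludes an early group comparison.

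**A reader might also conclude that the trial cannot reach 90% power.** That is too strong. The planned regression adjusts for the baseline value, and a moderate correlation can offset considerable loss. Adjusting for duration and sessions, which are tied to arm, could pull the other way. The article quantifies neither effect.

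**Loss and clustering values are assumptions.** Leaving treatment is not the same as missing an assessment. Clustering affects one arm, perhaps about half of it given the group capacity, and hardly matters at six months, when patients are in or just leaving the reception phase. All of this stands and limits how firmly any single power figure can be quoted.

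**A condensed article may leave the allowance for loss to a fuller document.** That would excuse silence. Here, however, the article fixes 212 as the number to be included and attaches 90% to it, and that pair reproduces only with no loss.

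**The figure of 41 treats 0.45 as a standardised change**, although it was chosen to size a group comparison. That is fair: 41 shows the mismatch and should not be adopted as a target.

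**Conclusion.** The mislabelling is certain: 158 is the between-group size at d = 0.45 and 80% power, and the article contains no basis for a within-subject size. The early processing is announced but has no defined test, purpose or error control. The 7.4% type I error applies only if the groups are compared at 158 and again at 212, each at 5%.

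The 90% for 212 is correct arithmetic for an unadjusted t-test with all 212 analysed and independent, with one patient per arm to spare. Outside that case it is unknown. Over assumed losses of 20–30% and no clustering, it runs from 78–83% unadjusted to 88–92% at a baseline correlation of 0.5. Clustering lowers each of these. The article supplies no loss rate, correlation or ICC, so none of these figures can be called the trial's true power.

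**What to change.** - Keep 212.
- Relabel 158 (79 per group) as the between-group size for 80% power at d = 0.45, or delete it.
- State that processing before the full sample is limited to within-arm or pooled psychometric analyses, with no between-group outcome comparison. If an early comparison is wanted, specify it and its alpha control in advance.
- Restate the power as 90% only for an unadjusted t-test with all 212 analysed. Add the power at the expected evaluable number, showing the assumed loss, baseline-outcome correlation and ICC.
- Account for therapy group in the STP-BPD arm in the analysis, for example with a partially nested model that has a random effect for group in that arm only.

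The cost is a few sentences, one model term and restated figures. The stated power may look less favourable, and early between-group results are given up. Limitations and challenges already foresees statistical consultation at a later stage, so this can be settled there, provided that it is done before any early processing begins.

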### Treatments

#### The STP-BPD

In the STP-BPD at Eginition Hospital, people with borderline personality disorder can receive psychoanalytic psychotherapy (59), along with other psychiatric services such as psychiatric evaluation, counseling, medication therapy, and hospitalization if needed (28, 29). In addition to existing treatments, additional therapies (i.e., arts-based therapies) are offered (22). The program bases its integrative approach and clinical practice on Bion’s (60) container/contained model, aiming to establish a broad framework known as the *‘Psychodynamic setting’*. The stable and secure *‘psychodynamic setting’* acts as a receptive container, absorbing the intense projections and projective identifications of the BDP patients, their frequent acting-outs, and the countertransference reactions of the clinicians, and enabling thinking over time, helps the patient internalize the containment capacity (28, 29), which lowers acting-out episodes and improves clinical symptoms.

Central to this approach is its team-based nature, which provides a supportive environment for mental health professionals (61), reduces splitting among them, and enhances their containing function. To this end, weekly staff meetings are held.

As mentioned above, the Program has a stepped care approach with two different steps/phases of intervention:

1. *The reception outpatient clinic* is the initial phase of the intervention, through which BPD patients enter the program. First, psychiatric and psychological eligibility assessments are carried out. Then, for a period of 6–8 months, the reception outpatient clinic offers eligible patients psychoanalytically oriented therapy sessions (1 session per month), psychiatric management sessions, and, if indicated, pharmacotherapy (1 session per month). The first phase of the program, which adheres to a stepped care approach, aims to provide a *‘holding’* environment for patients, manage their ambivalence about therapy, and prepare them for the next phase, which offers intensive psychotherapy. The initial phase also allows for the mental health care of a large number of patients before the more intense interventions of the second phase are available. The capacity of the reception outpatient clinic is 50 patients. Crisis management for patients during phase 1 included visits to the Emergency Department of the Eginition Hospital.

2. *The second phase of the program consists of* sp*ecific interventions*. Clinical criteria (‘readiness for therapy’, self-harm, suicidality, emergency room visits, need for hospitalization, etc.) and availability (e.g., twice a year in therapy groups, once a year in the day hospital, while a small number of patients enroll each year in individual psychoanalytic psychotherapy) determine the assignment of patients to one (or more) of these interventions. The following specific interventions are available:

*Group psychoanalytic psychotherapy*: This is the main intervention, with a capacity of approximately 50 patients, in groups of 8–10 patients. It lasts for 3 years and offers one or two 90-minute sessions per week.
*Individual psychoanalytic psychotherapy*: capacity of 4–8 patients. It lasts for 2 years and offers one 45-minute session per week.
*Group or individual psychodynamic art therapy*: capacity of 4–12 patients. Last 2 years and offers one two-hour group session or one 60-minute individual session.
*Day hospital program*: The day hospital program can accommodate up to 9 patients. It includes a combination of group and individual psychotherapeutic interventions (psychoanalytic psychotherapy, art therapy, drama therapy) and psychiatric management. The day hospital program lasts 9 months. After their completion, the participants continued in group psychoanalytic psychotherapy for an additional 3 years.
*Parent groups or parent couples’ professional counseling*: parents of all-day hospital patients and a limited number of outpatients can participate in parent groups or parent couples’ psychoanalytic counseling. It lasts for one year and provides one 90-minute group or couples session per week.
*Psychiatric management and pharmacotherapy*, if required (1 session per month). Supervision is offered fortnightly for all psychotherapy interventions and weekly for psychiatric interventions.

During phase 2, in case of crisis, the patient contacts his/her psychotherapist or psychiatrist by telephone and, if necessary, goes to the emergency room of Eginition Hospital. In cases of hospitalization, the patient continues the program after discharge.

#### Treatment as usual

TAU includes psychiatric management, counseling and pharmacotherapy (if needed) in the two outpatient clinics for BPD patients (TAU1 and TAU2). The TAU offers one 30-minute session per month. In the event of a crisis, patients contact their psychiatrist during working hours, or after that, they leave a message on the telephone answering machine and, if necessary, go to the Emergency Department of the hospital on duty. As mentioned above, both TAU centers were set up for the purposes of the study to ensure good treatment-as-usual service. They accept only patients with borderline personality disorder, the patients attend regularly (one session per month), and they can contact their doctor directly. These characteristics distinguish TAU centers from other outpatient departments in Greek public psychiatric hospitals, which observe patients across the full spectrum of psychopathology, where psychiatrists are usually not easily accessible, the appointments are made by a telephone operator or a secretary (not by the attending doctor), and sessions are infrequent (usually one session every two or three months).

## Evaluation of clinical effectiveness

### Assessments and clinical outcome measures

Two central research assistants with experience from previous clinical studies received standardized training in the outcome interviews. Training included 3 interview sessions as observers and 2–3 interview sessions under live supervision. When the researchers conducted the interview correctly and the differences in ratings did not exceed 1 point for 3 different items (46), we considered them trained to make independent assessments.

The central research assistants in turn trained a small group of research assistants at each participating center. Throughout the study, the central research assistants guide the research assistants, oversee the scheduling and flow of the assessments, collect and enter data, and ensure the validity of the assessments (62).

The instruments that were not available in the Greek language were translated. Two bilingual speakers (Greek/English) independently translated the instruments into Greek for this purpose, producing a matched version. A professional bilingual translator reverse-translated the agreed-upon version. The back translation was checked for consistency with the original translation. Any inconsistencies were reviewed in consensus meetings and appropriately adjusted. The Greek versions of the above instruments are currently undergoing psychometric property testing. At baseline, the Early Trauma Inventory-Short form (63) will be administered.

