## Methods and design

### Design

We will conduct our study in a naturalistic–pragmatic design, replicating everyday clinical practice conditions and thereby enhancing its external validity (50, 51). The evidence suggests that well-designed naturalistic studies, compared with RCTs (52–54), can provide evidence without overestimating effect sizes (internal validity), and they can address difficult-to-investigate trial questions, such as those related to public sector services (25). The study is a quasi-experimental pragmatic trial with two groups: an intervention group and a treatment as usual (TAU) group. The treatments for both groups (the intervention group and the TAU group) will be provided at public health hospitals. The intervention group will attend the STP-BPD of the 1^st^ Department of Psychiatry, Medical School, National and Kapodistrian University of Athens, Eginition Hospital. The TAU group will take place in two centers: the Outpatient Clinic for Borderline Personality Disorder Patients of the 2^nd^ Department of Psychiatry Medical School, the Attikon General University Hospital of the School of Medicine (TAU1), and the Outpatient Clinic for Borderline Personality Disorder Patients of the Psychiatric Clinic of the Sismanogleion General Hospital (TAU2). The study established both TAU centers, as detailed below.

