### Primary outcome measures

The primary outcome measures include the severity of BPD and severe parasuicidal behavior. 331 The BPDSI (Borderline Personality Disorder Severity Index-Leibniz Institute for Psychology) (64) is a semi structured clinical interview measure that captures specific BPS symptoms over the past three months. It contains 70 items, which are similar to the DSM-IV criteria. It covers nine areas of symptoms: *(1) abandonment; (2) interpersonal relationships; (3) identity; (4) impulsivity; (5) parasuicidal behavior; (6) affective instability; (7) emptiness; (8) outbursts of anger; and (9) dissociation and paranoid thoughts* (64). For its reliability, the internal consistency is greater than alpha = .90 (total score) or between alpha = .49 and.89 (subscales) (65). It is a reliable and valid instrument that is suitable for use as an outcome measure (64, 66). In our sector’s validation procedure of the BPDsi (67, 68), the statistical analyses revealed a fairly valid and reliable tool (Cronbach’s α = .99). A cutoff score of 15 between patients and controls has been established; thus, a score below 15, which is rated two years after randomization or earlier and maintained until follow-up, is used as a criterion for recovery (64).

**Suicide and Self-Harm Inventory** (69): The purpose of the interview is to collect accurate data about attempted suicides and self-harm incidents over a six-month period without attempting to measure their severity. Bateman and Fonagy (70, 71) define parasuicidal behavior as including three types of behavior: *1) suicide attempts (which must be intentional, life-threatening, and require medical intervention); 2) life-threatening self-harm behaviors (which must be intentional, cause visible tissue damage, and require nursing or medical intervention); and 3) admissions to a psychiatric hospital*. The Greek version will be used here (72).

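### Raters are organised by centre and each centre delivers one arm, so if local assistants rate local patients, rater differences on the BPDSI cannot be separated from the treatment effect

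*Protocol article*

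**What the plan says.** Under Primary outcome measures, the BPDSI "is a semi structured clinical interview measure that captures specific BPS symptoms over the past three months". The second primary measure, the Suicide and Self-Harm Inventory, is also an interview: "The purpose of the interview is to collect accurate data about attempted suicides and self-harm incidents over a six-month period", and it does not attempt to grade severity.

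Under Assessments and clinical outcome measures, two central research assistants were trained and certified first. The criterion was that "the differences in ratings did not exceed 1 point for 3 different items (46), we considered them trained to make independent assessments". Then: "The central research assistants in turn trained a small group of research assistants at each participating center". Oversight continues after that: "Throughout the study, the central research assistants guide the research assistants, oversee the scheduling and flow of the assessments, collect and enter data, and ensure" that the assessments are valid.

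Under Design, each centre belongs to one arm. For the specialised service: "The intervention group will attend the STP-BPD of the 1^st^ Department of Psychiatry, Medical School, National and Kapodistrian University of Athens, Eginition Hospital". For the comparator: "The TAU group will take place in two centers", namely Attikon and Sismanogleion.

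Under Evaluation of effect, each outcome is regressed on group with its baseline value, treatment duration, sessions attended and the variables that differed at baseline. No rater or centre term is listed. Limitations and challenges discusses selection, confounding, additional therapies, inception bias and performance bias, but not rater or detection bias.

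**The concern.** A semi-structured interview leaves scoring judgement to the interviewer. Teams that work at different centres can drift apart in how they probe and score, and assistants working beside a service may come to expect its patients to improve. In most multicentre trials such differences cancel, because every centre contributes patients to both arms. Here they cannot cancel if ratings are done locally: one team would rate all the specialised-service patients and other teams all the usual-care patients.

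A rater or centre term would not help under that arrangement. The two usual-care teams could be compared with each other, but the contrast between the Eginition team and the usual-care teams would coincide with the arm contrast. The remedy therefore has to lie in how interviews are assigned and cannot be left to the analysis.

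The reliability figures quoted for the BPDSI are internal-consistency coefficients. They say nothing about agreement between raters. The 1-point agreement criterion is stated for the two central assistants only, not for the centre assistants or between centres.

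**Working it through.** **Inputs from the protocol article.** 106 per group, d = 0.45 and power 0.90 (Sample size); two-sided 5% level (Dropout rates, last paragraph); baseline score as a covariate (Evaluation of effect).

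**Inputs assumed.** The size b of a spurious between-arm rating shift, in SD units, and the correlation rho between baseline and follow-up scores. The article gives neither.

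**The plan's own figure.** n per group = 2 × (1.960 + 1.282)² / 0.45² = 103.8, so 104 by the normal approximation. The t-test gives 104.7, so 105. The stated 106 is consistent with this, with power 0.906 (normal) or 0.903 (t). The sample size is not in question.

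**Scale.** Without adjustment, se = √(2/106) = 0.137, so the smallest significant observed difference is 1.96 × 0.137 = 0.27 SD. A shift of 0.20 SD is 0.20/0.45 = 44% of the design effect.

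**False-positive rate with no true effect.**

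Rate = 1 − Φ(1.96 − bias/se) + Φ(−1.96 − bias/se)

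With baseline adjustment, se = √[(2/106)(1 − rho²)]. At rho = 0.5 this is 0.137 × √0.75 = 0.119. Two cases bracket the problem:

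- *Stable shift*, the same at baseline and follow-up: bias = b(1 − rho). For b = 0.20, bias = 0.10 and bias/se = 0.84. Rate = 1 − Φ(1.12) + Φ(−2.80) = 0.134.
- *Shift at follow-up only*: bias = b. For b = 0.20, bias/se = 1.68. Rate = 1 − Φ(0.28) + Φ(−3.64) = 0.390.

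| Assumed shift (SD) | No adjustment | Adjusted, stable (rho 0.5) | Adjusted, follow-up only (rho 0.5) |
|---|---|---|---|
| 0.10 | 11.3% | 7.0% | 13.4% |
| 0.20 | 30.7% | 13.4% | 39.0% |
| 0.30 | 58.9% | 24.3% | 71.3% |

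For b = 0.20 and rho between 0.3 and 0.7, the rate is 19% down to 9% for a stable shift, and 33% up to 53% for a follow-up-only shift. Adjustment thus works in opposite directions: it absorbs part of a stable shift, but by shrinking the standard error it makes a late-arising shift more likely to reach significance.

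The calculation treats the BPDSI score as continuous and ignores the other covariates in the planned model. It does not describe the self-harm inventory, which records incidents.

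**The case against.** The strongest reply is that the premise is inferred. The article says where assistants were trained, not who rates whom. The two central assistants are qualified to rate independently and oversee scheduling everywhere, so they may do some of the interviews. A reader might infer that rater and arm are completely confounded, or that every rater knows the arm. The text states neither, and the point is therefore conditional.

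Second, this is a condensed article. Rater rosters, masking and reliability checks may be set out in the full protocol. That is fair as to their absence alone. The point rests on what the article does fix: rater teams by centre, and one arm per centre.

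Third, one central pair trains and supervises all the teams. This is a real standardising mechanism and should reduce drift. As described, however, it includes no cross-centre agreement check, and it does not by itself break the link between team and arm.

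Fourth, the self-harm inventory leaves less room for leniency, since its categories depend on medical or nursing intervention or on psychiatric admission. This stands, and the point is confined to the BPDSI.

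Fifth, a reader might take the unadjusted 31% as the error rate of the planned analysis. It is not, because the planned model adjusts for baseline. The adjusted figures are the relevant ones.

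Sixth, several secondary outcomes are self-reported, so an effect seen only on the BPDSI would be noticeable. That is a partial check. It would raise suspicion but could not correct the primary estimate.

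**Conclusion.** The point holds conditionally. As described, rater teams follow centres and centres follow arms, with central training and oversight but no stated masking, crossing or between-centre check. If local assistants rate local patients, a rating difference on the BPDSI cannot be told apart from a treatment effect, and no analysis can recover the distinction. Baseline adjustment reduces a stable difference and leaves a late-arising one intact.

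At an assumed 0.20 SD shift and rho of 0.5, the false-positive rate is about 13% (stable) or 39% (follow-up only) instead of 5%. The shift size and the correlation are assumptions, so these figures show how sensitive the contrast is. They do not estimate a bias known to exist.

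**What to change.** In Assessments and clinical outcome measures:

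- State who conducts the BPDSI interviews for which patients.
- Using the existing central and centre assistants, schedule BPDSI interviews so that raters see patients from both arms where feasible, with the central assistants covering a share at every centre. Keep the interview mode the same in both arms.
- Have all assistants score one shared set of recorded interviews to the 1-point standard already stated, at the start and periodically.
- Record rater identity at every interview.

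In Evaluation of effect, add rater to the BPDSI models once raters are crossed. Where crossing is not achieved, name rater and detection bias in Limitations and challenges.

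The cost is mainly scheduling and some travel. Some unmasking will remain, because patients may reveal their service. For patients already enrolled, crossing may change the rater between baseline and follow-up, which weakens what baseline adjustment can absorb. Moving every follow-up interview to an off-site rater is not asked for: with 212 patients and ten follow-up points that is up to 212 × 10 = 2,120 interviews, and the article gives no staff numbers that would show it to be feasible.
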